### Economic evaluation

The economic evaluation will gather information on the costs to the NHS, other government agencies and wider society of the interventions in the two arms of the RCT. The primary cost-effectiveness analysis will compare incremental differences in NHS (including LP referral costs) and other public sector costs with any health gains achieved over 12 months, measured in QALYs. We will estimate the net monetary benefit of specialist medical care plus the LP compared to specialist medical care alone and quantify uncertainty using confidence intervals, cost-effectiveness acceptability curves and sensitivity analyses [27]. In secondary analyses we will tabulate the wider costs, including travel and productivity costs and consequences, including school time missed, in a cost consequence study [28,29].

### Qualitative research

A process evaluation, drawing on qualitative research methods, will be undertaken to assess the implementation, acceptability and setting of the intervention as well as to explore users’ and practitioners’ views and experiences of both the intervention and outcomes.

#### In-depth interviews

Interviews with parents and children/young people were conducted at three time points for the feasibility study: after initial assessment but prior to randomisation, after randomisation but prior to the intervention and after the intervention. Analyses of data will continue from the feasibility study, supplemented with further in-depth interviews undertaken with some parents and children after the intervention to further assess their experiences of the trial and intervention. Interviews will be semi-structured in that they will follow a checklist of topics to ensure consistency, but parents and children will be able to raise issues of importance. Interviews will explore the recruitment process, including views and experiences of the initial assessment and recruitment to trial appointments, the written and verbal information provided to potential participants and its acceptability, and reasons for accepting or declining participation; beliefs, expectations and preferences about interventions in the early stages of the trial, and experiences of interventions and outcome later on; and prior exposure and external influences to the intervention that might impact upon its implementation and effectiveness.

#### Recording of recruitment to trial consultations

All recruitment consultations will be audio-recorded to document the interaction between recruiter and potential participant to explore information provision, recruitment techniques, patient treatment preferences, and randomisation decisions to identify recruitment difficulties and support change. This novel method can provide essential information about the way the study and its interventions are perceived as well as optimising methods for recruitment and design. It has proved crucial in evaluating information exchange and improving informed consent and rates of randomisation/acceptance of allocation in previous studies [30-32].

#### Observations

We will analyse observation data already collected on a small number of interventions, specialist medical assessments and specialist medical treatment follow-up sessions observed by the qualitative researcher to assess the implementation, acceptability and setting of intervention/treatment provision. Detailed notes have been taken, including the context, intensity and variability of intervention/treatment delivery, to understand how intervention/treatment is delivered and received in practice and to help interpret outcome results (for example, variations of effects in subgroups). All intervention sessions were audio-recorded, with consent, for monitoring purposes. We may observe further sessions if necessary following analysis of existing data. The final number of observations will be determined by data saturation, although up to ten observations in total are anticipated.

#### Qualitative data analysis

Analysis will be an ongoing and iterative process commencing soon after data collection. It will build on data analysed from the feasibility study and will inform further sampling and data collection. Interview transcripts and observation notes will be imported into NVivo (QSR International) [http://www.qsrinternational.com/products_nvivo.aspx: 2011] where they will be systematically assigned codes and analysed thematically to identify themes using techniques of constant comparison. Individuals exhibiting contrasting attitudes (‘negative cases’) will be studied in detail to understand reasons underlying such contrasts and to gain a deeper understanding of the data and findings. Throughout analysis, the perspectives of the individuals will be paramount, with careful account taken of the context within which the discussion takes place. Descriptive accounts will be produced, and theoretical explanations for behaviours, opinions and decisions will be developed.

Content analytic methods will be used to describe in a structured manner what was said by whom and how often in the consent to randomisation appointments. More flexible grounded theory methods (as in the interviews above) will be applied to identify common or divergent themes, particularly focussing on the impact of statements by the recruiter on patients. Conversation analysis will be used to focus in great detail on certain sections of the transcripts, for example the interactions during which randomisation is offered.

### Data protection

Children and young people are allocated a unique 13 digit identification number made up of the centre number, the team number, an individual patient number, first four digits of the postcode, and patient initials. This number is assigned to the patient and is used on assessment forms prior to transfer of data so they are anonymised at source. A list of names and corresponding identification numbers are kept separately and securely on a password protected NHS server.

Audio-recordings will be encrypted, password protected and stored on a secure university server for five years. This is to enable us to check recordings if necessary while reports are being written. Transcripts will be anonymised and secure password protected university server.

### Data monitoring

The data monitoring group will receive notice of serious adverse events (SAEs) for the sample as whole. If the incidence of SAEs of a similar type is greater than would be expected in this population, it will be possible for the data monitoring group to receive data according to trial arm to determine any evidence of excess in either arm.

Primary outcome data at six months will be examined once data are available from 50 patients, to ensure that neither arm is having a detrimental effect on the majority of patients. An independent statistician with no other involvement in the study will investigate whether more than 20 participants in the study sample as a whole have experienced a reduction of ≥ 30 points on the SF-36 at six months. In this case, the data will then be summarised separately by trial arm, and sent to the data monitoring group for review. This process will ensure that the trial team will not have access to the outcome data separated by treatment arm.

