### Randomisation

The recruiting researcher will explain the rationale for the study and its design, the uncertainties about the effectiveness of either intervention, the known advantages/disadvantages of the interventions, the options available outside the RCT, and the right not to take part in the study or to withdraw at any time. Willingness to participate will be ascertained, checking that both the young person and their family understand the study. Those willing to take part in the study will be asked to consent to randomisation and sign the consent form. The recruiting researcher will then telephone the automated randomisation service operated by the Bristol Randomised Trials Collaboration for the intervention allocation, which will be conveyed to the participant. Allocation will be minimised [15] by age and gender, and retain a random component to reduce risk of prediction of allocation. If for any reason the service is unobtainable, randomisation will be completed during the next working day and the participant will be told of the results by phone or in person.

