### ‘Outcome assessment’

The following self-completed inventories will be collected at the first clinical assessment (baseline), 3, 6 and 12 months: 11 item Chalder Fatigue Scale [17]; pain visual analogue scale; physical function short form (SF-36) [18]; the Spence Children’s Anxiety Scale (SCAS) [19]; the Hospital Anxiety and Depression Scale (HADS) [20] for children aged 14 and over, and the Euroqol (EQ-5D) [21] a five-item quality of life inventory. Children and young people are asked about school attendance and home tuition in a two-item inventory. We will ask for consent to check school attendance using school records at assessment, 3, 6 and 12 months. Follow-up questionnaires will be sent in the post with a stamped addressed envelope for self completion.

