#### Primary outcome

The primary outcome will be the SF-36 physical function subscale analysed as a continuous variable collected at six months post-randomisation. The SF-36 will be scored as the sum of responses to the ten items, each of which is coded 0 for ‘Yes, limited a lot’, 5 for ‘Yes, limited a little’ and 10 for ‘No, not limited at all’. This yields a score varying from 0 (for the highest level of disability) to 100 for no disability. The SF-36 physical function subscale will be used as we are primarily interested in change in physical function. It has been used in studies of adolescent CFS/ME [22] and in CFS trials in adults [16]. We chose six months as this was the first time that all those randomised to LP and SMC will have received LP. Secondary outcome measures will be school attendance, calculated as a percentage of expected sessions, at 3, 6 and 12 months; the SF-36 (physical function) at 3 and 12 months; the Chalder Fatigue Scale score at 3, 6 and 12 months; pain visual analogue scale at 6 months and quality adjusted life years (QALYs, derived from the EQ-5D) over the 12 month follow- up period.

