### Statistical considerations

#### Sample size

We used a definition of a clinically important difference for the SF-36 physical function subscale from three expert consensus panels for chronic diseases in adults. The panels conducted a literature search and used the Delphi technique to reach consensus on the thresholds for change over time for small, moderate and large clinically important SF-36 change scores [24]. Consensus was agreed by each panel that a small clinically important difference would be 10 as this is the equivalent to two state changes (a state change is one improvement in one item - the minimum difference between inventories). A moderate improvement was defined as 20 and a large improvement as 30.

To be able to detect a difference between the two treatment arms of 8 to 10 points on the SF-36 PCS at six months with 90% power and 1% two-sided alpha, we have calculated (using STATA) that a total of 32 to 50 participants in each arm for analysis are required. Allowing for 10 to 20% non collection of primary outcome data at six months, we aim to recruit 80 to 112 participants to the study.

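### The six-month safety look counts only children with a six-month SF-36, so a large fall already recorded at three months is not seen if the child then goes missing or withdraws

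*Protocol article*

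**What the plan says.** The Data monitoring section of the protocol article sets one numerical rule for the outcome data. On timing it says "Primary outcome data at six months will be examined once data are available from 50 patients". The purpose is "to ensure that neither arm is having a detrimental effect on the majority of patients". An independent statistician checks whether "more than 20 participants in the study sample as a whole" have had "a reduction of ≥ 30 points on the SF-36 at six months". Only if so are the data split by arm and passed to the data monitoring group. The section gives no rule for a child who has passed six months without a score.

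Other sections bear on this:

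- ‘Outcome assessment’: "The following self-completed inventories will be collected at the first clinical assessment (baseline), 3, 6 and 12 months". The inventories listed include the SF-36 physical function form.
- Primary outcome: the secondary outcomes include "the SF-36 (physical function) at 3 and 12 months". Six months was chosen because by then every child in the LP arm should have had the course.
- Sample size: "Allowing for 10 to 20% non collection of primary outcome data at six months", the recruitment target is 80 to 112.
- Randomisation: families are told of "the right not to take part in the study or to withdraw at any time".
- Non-responders: a reminder carries a reduced set that includes the SF-36, followed by an offer to complete that set by telephone.

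**The concern.** The event is defined by a score at a single visit, and the look waits for 50 such scores. A child with no six-month score therefore cannot be an event, whatever is known about that child. The SF-36 is also collected at three months, so for some of these children a fall of 30 points or more may already be on file. The rule does not use it.

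This matters most if non-collection is related to worsening. The count would then be taken in a group from which some of the children it is meant to find have been removed. The participants are children, and the Background says no reported study has examined possible side effects of LP. A harm check should not depend on missing scores being unrelated to harm when a partial check is available from data already held.

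**Working it through.** **Inputs.** From Data monitoring: 50 children with six-month data, a trigger of more than 20 (so at least 21), and an event of a fall of 30 points or more at six months. From Sample size: non-collection d of 10 to 20%, and 32 to 50 children per arm for analysis.

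**1. The protocol's own use of the allowance.** Recruitment = N/(1 − d).
- 2 × 32 = 64; 64/0.80 = 80.
- 2 × 50 = 100; 100/0.90 = 111.1, rounded up to an even 112.

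This reproduces 80 to 112, so the allowance is meant as the share of randomised children with no six-month primary outcome. Its natural reading is what remains after the Non-responders procedure.

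**2. Children outside the count.** Children due = 50/(1 − d).
- d = 10%: 50/0.9 = 55.6, about 56 due, 6 not counted.
- d = 20%: 50/0.8 = 62.5, about 63 due, 13 not counted.

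Against the 21 falls needed, that is 6/21 = 29% to 13/21 = 62%. These figures treat the allowance as realised and the chase as complete when the fiftieth score arrives.

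**3. When the missing children would change the outcome.** If h uncounted children had a qualifying fall, the trigger is missed because of them only when the observed count lies from 21 − h to 20. The documents do not give h, so the range is shown:
- h = 3 (half of 6): 18 to 20 observed falls.
- h = 6 (all of 6, or just under half of 13): 15 to 20.
- h = 13 (all of 13): 8 to 20.
- h = 0: no effect.

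**4. Trigger probability under assumed fall rates.** As written, P(X ≥ 21) with X ~ Bin(50, p). If falls in the m unscored children were also known and counted, the probability is the sum over k of P(K = k) × P(X ≥ 21 − k), with K ~ Bin(m, q). All values of p and q are assumptions.

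| Fall rate: scored p / unscored q | As written (50) | 6 added (56) | 13 added (63) |
|---|---|---|---|
| 20% / 20% | 0.000 | 0.002 | 0.009 |
| 20% / 60% | 0.000 | 0.015 | 0.207 |
| 30% / 30% | 0.048 | 0.141 | 0.325 |
| 30% / 60% | 0.048 | 0.288 | 0.731 |
| 40% / 40% | 0.439 | 0.695 | 0.888 |
| 40% / 60% | 0.439 | 0.800 | 0.971 |

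Two things follow. First, where p = q the probability still rises, only because more children are counted against a fixed number. At 30%, that takes 0.048 to 0.141 or 0.325 with no informative missingness at all. Second, the last two columns are upper bounds on what three-month scores could recover, because not every unscored child will have one or will have fallen by then.

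**The case against.** The case against is substantial, and much of it stands.

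- **Missing children are not entered as non-events.** A reader might infer that each one counts as a child without a fall. That is not so: the look waits for 50 observed scores, and the missing children lie outside those 50. Understatement in the scored group needs informative missingness, which the documents do not assert.
- **No arm looks safer at this stage.** A reader might infer that the arm with more drop-out is flattered. The trigger count is pooled, and arms are separated only after it is met.
- **Silence is not evidence.** A reader might infer that the data monitoring group learns nothing about withdrawals. The article condenses a fuller protocol, and a charter may provide for this. What can be said is that the rule spelled out here does not include it.
- **It is not the only contact through which harm could surface.** Interventions describes SMC appointments and LP follow-up calls, and the Discussion promises close follow-up. The look is the only numerical rule shown for non-serious worsening, and the article gives no route from those contacts to the data monitoring group.
- **Non-response is pursued.** Telephone scores count, so the gap concerns only children still unscored afterwards and those who withdrew. The 10 to 20% is a planning allowance, not a forecast.
- **Three-month scores are imperfect.** Some LP-arm children may not have had the course by three months, and a fall may recover by six.

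What remains is narrow. The article states timing, event and threshold explicitly, and on those terms a fall already on file at three months is ignored when the six-month score is missing.

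**Conclusion.** The point holds as a cheap improvement to the safety look, not as an error or contradiction. By the wording of the rule, children without a six-month SF-36 cannot enter the count, and three-month scores play no part. At the protocol's own allowance this affects about 6 to 13 children when 50 are scored.

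Whether harm is understated depends on worsening children being missing more often, which is an assumption. Even then the decision changes only when the observed count is below 21 by no more than the number of hidden falls. How many unscored children would have a three-month score showing the fall cannot be estimated from the documents.

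**What to change.** Leave the six-month count and its trigger as written, and add two items to the independent statistician's task:

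1. A supplementary count, reported separately, of children who have passed six months without a six-month score and whose last available SF-36, at three months, was 30 points or more below baseline. Mark each by whether LP had been received by then.
2. A by-arm table sent to the data monitoring group whether or not the trigger is met: children due at six months, scored (by post or telephone), not scored, and withdrawn, with any stated reason.

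The two counts must not be added together against the fixed threshold of 20, because a larger number counted raises the trigger rate by itself, as the equal-rate rows of the table show. The supplementary count should carry the caveat that a three-month fall may precede LP or may have recovered by six months.

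The cost is a few sentences of text and a short tabulation from data already collected, by a statistician already assigned to the look. The data monitoring group would receive return and withdrawal numbers by arm in every case, which goes beyond the present conditional release. The trial team stays blind to arm.

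### The SF-36 harm check at 50 patients is meant to protect each arm but is triggered by a pooled count, so harm to a bare or moderate majority of one arm would probably not trigger it

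*Protocol article*

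**What the plan says.** The Data monitoring section of the protocol article sets out the check in full.

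- **Timing:** "Primary outcome data at six months will be examined once data are available from 50 patients".
- **Purpose:** "to ensure that neither arm is having a detrimental effect on the majority of patients".
- **Test:** an independent statistician determines "whether more than 20 participants in the study sample as a whole have experienced a reduction of" at least "30 points on the SF-36 at six months".
- **Consequence:** "In this case, the data will then be summarised separately by trial arm, and sent to the data monitoring group for review".

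The stated benefit of this process is that the trial team does not see outcome data by arm. The same section has a separate route for serious adverse events (SAEs). These are notified for the whole sample, and if events of a similar type exceed what is expected, "it will be possible for the data monitoring group to receive data according to trial arm to determine any evidence of excess in either arm".

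The article gives no derivation of the figure of 20, no expected rate of 30-point falls and no count within an arm.

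**The concern.** The purpose names neither arm, which is most naturally read as a condition on each arm taken separately. The test counts events over both arms together, and that count decides whether the data monitoring group sees any SF-36 data by arm. When one arm does badly and the other does not, the unharmed arm contributes few events and the pooled count stays low. That is the pattern the stated purpose is about.

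The participants are aged 12 to 18, and the Background section says that no studies of the effectiveness or possible side effects of the Lightning Process have been reported. If the trigger stays silent, the trial may be taken to have passed a check that neither arm harms most of its children, when the check had little chance of showing otherwise.

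**Working it through.** **Inputs**

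- Look at 50 patients; trigger is more than 20, so at least 21; event is a fall of 30 points or more (Data monitoring).
- Arm sizes: the allocation ratio is not stated. Sample size says "a total of 32 to 50 participants in each arm for analysis are required", which implies equal arms, so I assume 25 and 25. Allocation is by minimisation with a random component (Randomisation), so the split is approximate and I vary it.
- Rate of 30-point falls in the unharmed arm: not given. I use 0%, 5%, 10% and 20%.

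The protocol states no operating characteristic for the trigger, so there is no figure of its own to reproduce.

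**Step 1: direct count.** The pooled threshold is 21/50 = 42%. A majority of an arm of 25 is 13 (13/25 = 52%). With 13 events in one arm and none in the other, the count is 21 − 13 = 8 short. With 20 of 25 (80%) and none in the other, it is still 1 short. With events in one arm only, the trigger needs 21/25 = 84%.

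**Step 2: other splits, no events in the other arm.** The required share is 21 divided by the arm size: 21/22 = 95%, 21/24 = 88%, 21/26 = 81%, 21/28 = 75%.

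**Step 3: events in the other arm.** With *k* events there, the harmed arm needs (21 − *k*)/25. For *k* = 1, 3, 5 and 8 this is 80%, 72%, 64% and 52%. So 8 of 25 children (32%) in the other arm must also fall 30 points before a bare majority in the harmed arm triggers the check. Conversely, 11 of 25 (44%) plus 10 of 25 (40%) does trigger it with no majority in either arm.

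**Step 4: probability that the trigger fires.** Let X₁ ~ Bin(25, p) in the harmed arm and X₂ ~ Bin(25, q) in the other, independent. P(trigger) = P(X₁ + X₂ ≥ 21), by exact convolution:

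| Rate in other arm, q | p = 52% | p = 60% | p = 70% | p = 80% |
|---|---|---|---|---|
| 0% | 0.001 | 0.01 | 0.09 | 0.42 |
| 5% | 0.01 | 0.06 | 0.25 | 0.64 |
| 10% | 0.04 | 0.15 | 0.43 | 0.79 |
| 20% | 0.22 | 0.43 | 0.74 | 0.95 |

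**Step 5: comparison, for illustration only and not a proposed rule.** Counting at least 13 of 25 within the harmed arm gives P(X₁ ≥ 13) = 0.58, 0.85, 0.98 and more than 0.99 at the same four values of p.

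**Minor remark on the event.** The score runs from 0 to 100 (Primary outcome), so a child with a baseline below 30 cannot fall by 30 points and can never count. The article does not say how many such children to expect.

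**The case against.** Four points can be made for the plan.

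**The 84% is the worst case.** It needs an even split and no events in the other arm. In a fluctuating illness some 30-point falls may occur under either treatment, and the table shows the trigger improving as that rate rises: at 20% in the other arm it fires with probability 0.74 and 0.95 for true rates of 70% and 80%. This stands. A reader might infer that the check cannot detect one-arm harm, or would almost never open the data by arm. The figures do not support that once the harmed arm has a large majority affected. They do support weakness near a bare majority: at 52% the probability does not exceed 0.22 anywhere in the range shown.

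**It is not the only look at harm.** The SAE route can also release data by arm, so the 84% applies to the SF-36 check alone. This stands too, but the route does not clearly close the gap, because nothing in the article says that a 30-point fall in SF-36 is an SAE.

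**Pooled review of SAEs is a legitimate choice.** A reader might extend the criticism to it, since "The data monitoring group will receive notice of serious adverse events (SAEs) for the sample as whole". The documents do not support that. The SAE arrangement contradicts no aim stated for it, and a condensed article may leave the expected rates to the full protocol or a monitoring charter.

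**The wording of the aim is loose.** It speaks of the majority of patients without adding that these are the patients of each arm. The reference to neither arm makes the per-arm reading the natural one, but the text could be clearer.

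None of this removes the mismatch. The rule is stated in full, so it cannot be put down to detail left to another document.

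**Conclusion.** The concern holds for the SF-36 check. Its trigger does not measure what its stated purpose names. With 25 per arm and no 30-point falls in the other arm, 21 of 25 children (84%; 95% to 75% for a harmed arm of 22 to 28) must meet the criterion before SF-36 data are split by arm, against 13 for a majority. At a true rate of 60% in one arm the check is more likely to stay silent than to fire at every rate examined for the other arm, from 0% to 20%.

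The check is therefore unlikely to detect harm to a bare or moderate majority of one arm unless many children in the other arm also deteriorate. It can detect harm to a very large majority. The size of the problem rests on two assumptions that the article does not settle: near-equal arms at the look, and the rate of 30-point falls in the unharmed arm. The mismatch between aim and rule rests on neither.

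**What to change.** Reconcile the trigger with its purpose. At the 50-patient look, the independent statistician already named counts falls of 30 points or more within each arm and sends the by-arm counts to the data monitoring group in a closed report, without first requiring a pooled threshold. The data monitoring group sets the number that prompts action. The wording of the aim should say explicitly that it applies to each arm. The SAE arrangements need no change on this account.

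The cost is a change of protocol or charter wording and one extra table. No new data are collected and the trial team stays blind to arm-level outcomes, as now. The downside is that the data monitoring group sees arm-level outcome counts once even if nothing is wrong.

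### The six-month harm check has an arm-level aim but a pooled trigger of more than 20 large falls, so it cannot guarantee that harm to most of one arm is seen by arm

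*Protocol article*

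**What the plan says.** The Data monitoring section describes one look at outcome data: "Primary outcome data at six months will be examined once data are available from 50 patients". Its stated purpose is "to ensure that neither arm is having a detrimental effect on the majority of patients". A statistician who is otherwise uninvolved in the study then determines "whether more than 20 participants in the study sample as a whole have experienced a reduction of ≥ 30 points"; the falls counted are those in the six-month SF-36 score. What follows depends on that count: "In this case, the data will then be summarised separately by trial arm, and sent to the data monitoring group for review". The section adds that this keeps by-arm outcome data from the trial team. No by-arm look at SF-36 is described for a count of 20 or fewer.

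The same section has a separate route for serious adverse events: "The data monitoring group will receive notice of serious adverse events (SAEs) for the sample as whole". By-arm data can follow if events of a similar type exceed expectation. That route does not use SF-36 falls.

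**The concern.** The aim concerns each arm: neither should be doing harm to most of its patients. The rule counts both arms together, and the count decides whether anyone sees SF-36 data by arm. Harm confined to one arm is diluted by an unharmed comparator, so the rule is weakest in the pattern the aim describes.

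The participants are aged 12 to 18, and the Background says that no studies of the effectiveness or possible side effects of LP have been reported. This is the only safeguard in the article that uses outcome data. If it does not trigger, nothing has been established about either arm separately. The point concerns the pooled count only, not the 30-point size of fall, the timing of the look or the adverse-event rule.

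**Working it through.** **Inputs from the protocol article**
- Patients at the look: 50, both arms together (Data monitoring).
- Trigger: more than 20 falls of 30 points or more, that is at least 21; 21/50 = 42% (Data monitoring). No derivation of the 20 is given, so there is no calculation to reproduce.

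**Assumptions**
- Arm sizes: 25 and 25. The Randomisation section says "Allocation will be minimised [15] by age and gender, and retain a random component" but gives no ratio. The Sample size section, "a total of 32 to 50 participants in each arm for analysis are required", supports roughly equal arms. Splits from 20:30 to 30:20 are also checked.
- Rates of a fall of 30 points or more: the documents give none, so a range is shown.

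**Step 1: counts.** Let a and b be the falls in the two arms. The check triggers if a + b ≥ 21. With 25 per arm, the smallest majority is 13.
- If a = 13, there is no trigger when b ≤ 20 − 13 = 7.
- If b = 0, there is no trigger up to a = 20, and 20/25 = 80%. A trigger then needs a = 21, and 21/25 = 84%.

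**Step 2: other splits.** The same formula, with the majority in the arm of the stated size:

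| Size of harmed arm | Size of other arm | Majority | Falls in other arm that still give no trigger |
|---|---|---|---|
| 20 | 30 | 11 | up to 9 |
| 25 | 25 | 13 | up to 7 |
| 30 | 20 | 16 | up to 4 |

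With 20 in the harmed arm and no falls in the other, all 20 could fall without a trigger.

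**Step 3: chance of a trigger.** Take X ~ Bin(25, p_LP) and Y ~ Bin(25, p_SMC), independent. P(trigger) = P(X + Y ≥ 21), exact:

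| LP rate | SMC 0% | SMC 5% | SMC 10% | SMC 20% | SMC 30% |
|---|---|---|---|---|---|
| 60% | 0.9% | 5.5% | 14.7% | 43.5% | 72.4% |
| 70% | 9% | 25% | 43% | 75% | 92% |
| 80% | 42% | 64% | 79% | 95% | 99% |

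The calculation is symmetric, so the arm labels can be exchanged.

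**Step 4: silence when a majority of one arm has fallen.** At a true rate of 60%, P(X ≥ 13) = 84.6%. Given that X ≥ 13, the check stays silent with probability 93% if the other arm's rate is 5%, 83% at 10%, 49% at 20% and 19% at 30%.

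**Step 5: contrast.** If both arms share a rate of 40%, so that there is no majority and no difference between arms, P(trigger) = 44%. That is about the same as for 60% against 20%, and eight times the 5.5% for 60% against 5%.

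**The case against.** The strongest reply is that pooled-first review is a consistent choice. The same section handles serious adverse events that way, and it spares the monitoring group unblinded data unless there is reason for concern. The rule also works in some settings: it triggers when falls are common in both arms, or when at least 21 of one arm fall. With a 20% rate in the other arm it triggers 75% of the time at 70%, and 95% at 80%. All of this stands. It limits the size of the gap but does not make the rule match its stated aim. Nor does keeping the trial team blind require a pooled count, since an independent statistician already does the counting.

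It might be said that the aim refers to most of the 50 patients together. But the sentence speaks of the effect of either arm, and an arm can affect only its own patients. A majority of 50 would be 26, which is not the trigger either.

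A reader might infer three stronger things that the documents do not support:
- **That the check is useless, or silent whenever one arm is harmed.** The table in the working shows otherwise.
- **That no by-arm data of any kind could reach the monitoring group.** The adverse-event route may supply some, and the Discussion says families will be followed closely. What is missing below the trigger is SF-36 data by arm.
- **That the chance of a trigger is known to be about 1% to 5%.** Those values need an SMC rate of 0% to 5% and an LP rate of 60%, and no rates are given.

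**Conclusion.** The concern holds in this form: the stated aim is arm-level, the only trigger is pooled, and the trigger therefore cannot guarantee the aim. The counting argument needs no fall rates. With 25 per arm, 13 falls against 7 or fewer, or 20 against none, pass without any SF-36 data by arm reaching the monitoring group. Equal arms are an assumption, but the gap remains for every split examined from 20:30 to 30:20.

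How often this would happen does depend on assumed rates. For an LP rate of 60%, the chance of a trigger runs from 0.9% to 43.5% as the SMC rate goes from 0% to 20%; for 80% it runs from 42% to 95%. The gap is serious when large falls are rare in the other arm and modest when they are common. The primary analysis and its estimate are unaffected. Because this is a safeguard for children and is stated explicitly, it should be corrected rather than left to interpretation.

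**What to change.** Reconcile the aim and the trigger in the Data monitoring section in one of two ways:

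1. At the 50-patient look, the independent statistician sends the data monitoring group a confidential summary of six-month SF-36 falls by arm, whatever the pooled count.
2. If a gate is kept, apply it within each arm, at a level agreed by the sponsor and the data monitoring group.

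Under either option the trial team still sees nothing by arm.

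The change takes about one sentence and, under the first option, one extra table. The downside is small but real. The monitoring group would see the primary outcome, dichotomised, by arm, once. The Sample size section plans 32 to 50 per arm for analysis, so 64 to 100 in total; 50 patients are 50/100 = 50% to 50/64 = 78% of these. The text should say that no efficacy test is made at this look.
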